### ***Storage of Samples***

Patients will be asked for consent to store dried blood spots and leftover urine and serum samples after testing is complete. Blood and urine samples will be stored with no demographic or clinical data for future use at a specimen bank at the INLS Laboratory in Luanda. The samples will be stored with a code and without any personal information that could link them to the participant. Samples may be used for testing for infectious diseases, immune markers of infection or HIV phylogenetic. If a researcher wishes to use these specimens in a future survey, they will need to submit a research proposal to the INSP Ethics Committee who will act on the participants' behalf to weigh the risks and benefits of future testing of specimens, and whether the results can be linked to the coded questionnaire data from this survey. Participants can choose not to have their specimens stored and still be part of this survey.

#### ***D. RDS Survey Procedures***

##### ***Study Site***

The behavioral survey employing RDS methodology will be conducted at a public health center in Cabinda, a site known to the local population. At this site, private rooms will be provided for interviews and local coordination of the survey, with access restricted to the research team. This site will be designed to provide an inviting and comfortable environment for participants. Days and times of operation will be established after the start of field work. If necessary, alternative RDS sites (i.e. mobile van, participant's house, etc.) will be identified for participants who request more privacy. A field study coordinator will be responsible for managing the team and for ensuring compliance with all procedures described in this protocol. At least three interviewers, one receptionist, and one field coordinator will be at the study site during hours of operation.

If MSM and transgender women in any province cannot be effectively recruited through public sites, we will seek the assistance of community leaders and members in recruiting five to eight persons from the MSM and transgender community to serve as "seeds" or as persons who will recruit peers from their own communities via a system of recruitment invitations. The number of seeds may be increased if half of the recruitment chains fail to produce new recruits a month or two before data collection ends. We will attempt to identify a diverse (i.e. different age groups, ethnicities, socio-demographics, and education level) and popular (i.e., those having many network connections) group of seeds to start data collection.

##### ***Inclusion Criteria***

For the Cabinda study, female participants who meet the following eligibility criteria will be invited to participate in the project:

- At least one sexual contact for cash in the last 12 months
- At least 15 years of age at time of interview
- Resident of Cabinda province at time of interview
- Possession of a valid RDS coupon
- Consent to participate in a face-to-face structured behavioral survey

The interviewer will explain the study to the participant and ask for written informed consent (Appendix 9).

##### ***Peer Recruitment and Survey Participation***

We will have two types of participant through RDS: 1) seeds, who are the initial study participants recruited by field staff and investigators; and 2) new study participants recruited by previous study participants.

Each seed will receive three unique invitation coupons to be distributed to their peers which will constitute the first "wave" of the study. The number of seeds may be increased if recruitment slows or halts in the first month of data collection.

Times and locations where the invitee can participate in the study will be listed on the coupon (see Appendix 10) along with a telephone number of a field supervisor so that participants can call and schedule an appointment to participate.

All people who arrive with a coupon at a predetermined study time and place will be checked for eligibility. Interviews and testing will be conducted at sites convenient to participants and investigators. If eligible, team members will explain study procedures and ask participants to sign the informed consent form before administering a 20-25 minute standardized questionnaire on paper form or smartphone. HIV and STI testing and counseling will also be administered per the SADC study protocol and laboratory manual. As with site patrons and workers, the counselor will follow up with RDS participants testing positive for HIV or other STI to link them to additional health services in accordance with national guidelines.

After participating in the study, each participant will receive a gift, and three new coupons to give to their peers inviting them to participate in the study. Before receiving the three invitations, each participant will be trained on the peer recruitment process and be told to give one coupon to each of three friends, relatives or people they are close to, who are over 15, who are residents of Luanda, to whom they have seen or spoken to in the past 30 days and who received money for sex in the past 12 months. This process will be repeated until the sample size is achieved. After distributing their invitations to their peers, participants will return to collect their secondary incentives and will be asked to complete a non-response assessment to determine the number of invitations distributed, number of people who refused to accept the invitations, reasons given for refusing to accept the invitations, and type of relationship with each person they attempted to recruit (see Appendix 6).

Once 75% of the sample size is reached and equilibrium of the sample is achieved, the study supervisor may inform study staff to reduce the number of recruitment coupons dispensed to participants from three coupons to two coupons to one coupon. Determining when to end RDS recruitment will take several factors into consideration including the number of recruits still needed to reach the sample size, number of valid (unexpired) coupons still in the community, and average number of participants enrolling at the study site every day.

Various sociodemographic variables and type of sex work will be monitored during data collection to identify and prevent recruitment bottlenecks. Recruitment bottlenecks occur in RDS studies when participants recruit many peers with similar characteristics, such as youth or street-based sex workers. If it seems that during data collection, the sample will be heavily influenced by a particular subpopulation, the study coordinator and investigator can reduce or eliminate the number of coupons given to a particular recruitment chain. Investigators can also start new seeds that have characteristics that are underrepresented in the sample (such as telephone based sex workers) in an attempt to obtain a more representative sample.

As recruitment nears sample size, equilibrium of the sample will be assessed using RDSAT. If both sample size and equilibrium criteria are met, no new coupons will be distributed and the duration of the expiration periods will be narrowed to reduce the chances of persons trying to enroll in the study once it has ended. During every interview, all participants will be informed that no more interviews will be conducted once the sample size is reached. Furthermore, interview sites will have a protocol in place for explaining the termination of the survey to those who show up once the sample size is reached.

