### B. Study Populations

The study populations are sex workers, MSM and transgender women, at least 15 years of age who are residents of a to-be-defined geographic area at time of interview. International definitions of key populations follow:

- Sex worker (from the UNAIDS Guidance Note on HIV and Sex Work): “female, male and transgender adults and young people who receive money or goods in exchange for sexual services, either regularly or occasionally”. This definition includes those who occasionally exchange sex for gifts. It does not include people younger than 18.
- Men who have sex with men: MSM is an abbreviation used for ‘men who have sex with men’ or ‘males who have sex with males’. The term ‘men who have sex with men’ describes males who have sex with

males, regardless of whether or not they have sex with women or have a personal or social gay or bisexual identity. This concept is useful because it also includes men who self-identify as heterosexual but have sex with other men. However, abbreviations should be avoided whenever possible. Writing out the term is preferred.

- Transgender persons: ‘individuals whose gender identity and/or expression of their gender differs from social norms related to their gender of birth. The term transgender persons describes a wide range of identities, roles and experiences which can vary considerably from one culture to another.’

Operational population definitions and inclusion criteria will be established either through the mapping readiness assessment or during data analysis based on participants’ responses to the behavioral questionnaire.

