### ***RDS Population Size Procedures***

We will use the unique object multiplier method to obtain a population size estimate of female sex workers in the province of Cabinda. The multiplier method is the most commonly used population size estimation method, in part because it is relatively straightforward and utilizes simple calculations. The unique object multiplier method involves the distribution of a set number of unique objects, such as key chains, to members of the target population. Unique objects will be distributed widely at specific locations where female sex workers congregate (i.e. bars, brothels, hotels, etc.). The goal is to distribute as many unique objects as possible, but no less than the agreed upon study sample size.

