**The formula for estimating the population size using a multiplier is**

$$N = \frac{(n_1 \times n_2)}{m}$$

where N is the estimate of total population size; n1 is the number of individuals receiving unique objects; n2 is the number of individuals participating in the RDS; m is the number in both populations (i.e. the number of MSM who received unique objects and participated in the RDS)

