## **Assumptions**

Members of the sex worker, MSM or transgender population must have a chance of being included in both sources of data. Data from both sources will be evaluated for any potential barriers to inclusion of members of the target population. Where this assumption is violated, this will be clearly documented and reported, and other sources of data will be considered.

The multiplier method requires clear and consistent population definitions, time reference periods, and catchment areas between the different data sources. During preparation for implementation of multiplier activities and collection of unique object and survey data, these issues will be carefully considered, and investigators will ensure that definitions across data sources will be coordinated.

**Objective 8: To provide data to inform and guide future behavioral surveys and prevention strategies targeting sex workers, MSM or transgender women in Angola.**

Responses collected at a roundtable meeting with key stakeholders held at the end of data collection will be analyzed. We will invite all USG agencies, local NGOs, and key government officials to discuss how survey results can assist ongoing and future behavioral activities targeting sex workers, MSM and transgender women and how these results can advance priorities outlined in the Country Operating Plan (COP) and Angola's National Strategic Plan (NSP). Priorities for Local AIDS Control Efforts (PLACE) studies in identifying high transmission HIV/AIDS areas to improve HIV prevention program delivery. Combined data from objectives A, B and C will be used to guide the design of new prevention messages targeting sex workers, MSM and transgender women. All results will be shared with NGOs and other agencies working directly with sex workers, MSM and transgender women in Angola.

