| 4. Age (If <18 years old, do not give object.)               |                                                          |                                                          |                                                          |                                                          |                                                          |
| 5. Living in _____ (If no, do not give object.)                 |  Yes  No |  Yes  No |  Yes  No |  Yes  No |  Yes  No |
| 6. Is a female sex worker (If no, do not give object.)          |  Yes  No |  Yes  No |  Yes  No |  Yes  No |  Yes  No |
| Unique Object Distribution:                                     |                                                          |                                                          |                                                          |                                                          |                                                          |
| 7. Have already received [object] (If yes, do not give object.) |  Yes  No |  Yes  No |  Yes  No |  Yes  No |  Yes  No |
| 8. Accepted [object]                                                   |  Yes  No |  Yes  No |  Yes  No |  Yes  No |  Yes  No |

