### Instructions for using Size Estimation Field Staff Contact Log

- 1. Date:** Write the date of distribution activity.
- 2. Distribution Site:** Write the site in which the distribution activity is taking place.
- 3. Time:** Write the time of distribution activity.
- 4. Age:** If the person is under 15 years old, do not give object or collect any other information.
- 5. Living or working in Cabinda Province:** Ask question: *Do you live or work in Cabinda province?* If answer is no, do not give object or collect any other information.
- 6. Is a female sex worker:** Ask question: *In the past 12 months, have you had received money for sex?* If answer is no, do not give object or collect any other information.
- 7. Have already received [object]:** Ask question: *Have you received a [object] by a field staff member in the past two weeks?*
- 8. Accepted [object]:** Explain that these objects are being distributed for a survey and that the only participation needed from him in this survey is to accept the object and that no other questions will be asked. If the person accepts the object, ask him to keep the object because in about two weeks to four months, someone might ask them again if they have received this object.

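### Cabinda RDS survey: coupons are directed to Luanda residents, and objects go to women who only work in Cabinda although the survey admits residents only

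*Protocol*

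**What the plan says.** Three residence rules apply to the Cabinda work.

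- **Survey.** Section VI.D, Inclusion Criteria, requires a "Resident of Cabinda province at time of interview". Section VI.B likewise defines the study populations as "residents of a to-be-defined geographic area at time of interview".
- **Coupons.** Section VI.D, Peer Recruitment and Survey Participation, trains each participant to pass her three coupons to people "who are over 15, who are residents of Luanda, to whom they have seen or spoken to in the past 30 days" and who were paid for sex in the previous year.
- **Objects.** The printed log in Appendix 13 reads "Living in _____ (If no, do not give object". The instructions to the same log, item 5, have staff ask "Do you live or work in Cabinda province" and withhold the object only if the answer is no.

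The size estimate is N = n1 × n2 / m (Section VIII.C), where "n1 is the number of individuals receiving unique objects; n2 is the number of individuals participating in the RDS", and m is the number in both. Its stated purpose is to "obtain a population size estimate of female sex workers in the province of Cabinda" (RDS Population Size Procedures). The Assumptions paragraph says "The multiplier method requires clear and consistent population definitions, time reference periods, and catchment areas between the different data sources" and promises that the investigators will coordinate definitions across sources.

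**The concern.** These are operative field rules, and they disagree with each other. They create two separate problems.

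1. **Recruitment.** Someone who meets the coupon script's residence condition cannot meet the survey's. Everyone who arrives with a coupon is screened, and the coupon of a person screened is kept and stamped as used. A recruiter who follows the script therefore spends her coupons on ineligible people. She also earns no secondary incentive, since that depends on a recruit taking part.
2. **Size estimation.** The multiplier method tolerates objects reaching only some residents, provided that the survey represents residents. It does not tolerate objects reaching people whom the survey cannot sample. Such women raise n1 and can never raise n2 or m. Sizing the female sex worker population is a stated Cabinda objective, and the protocol intends size estimates as denominators for programme coverage.

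**Working it through.** The protocol gives no numerical size estimate for Cabinda and no formula behind its target of about 400 women, so there is no figure to reproduce. The check applies the protocol's own estimator and coupon limit.

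**Size estimate**

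Inputs from the protocol: N = n1 × n2 / m; n2 about 400 (Section VI.E); n1 at least the survey sample size, so at least 400 (RDS Population Size Procedures). Assumed: R resident sex workers, a survey that represents them, and a share f of objects given to women who work but do not live in the province.

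- Objects held by residents: n1(1−f).
- Expected overlap: m = n2 × n1(1−f) / R.
- Estimate: N = n1 × n2 / m = R / (1−f).

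For illustration, with R = 2000 (assumed) and n1 = n2 = 400:

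| f (assumed) | expected m | N | N / R |
|---|---|---|---|
| 0 | 80 | 2000 | 1.00 |
| 5% | 76 | 2105 | 1.05 |
| 10% | 72 | 2222 | 1.11 |
| 20% | 64 | 2500 | 1.25 |

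The ratio does not depend on R: R = 1000 and R = 4000 give the same factors. Simulated medians (20,000 hypergeometric draws per scenario) matched the table. A larger sample does not remove the error.

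**Which population is N?** If W non-resident workers exist and objects reach both groups at the same rate, then f = W/(R+W), and R/(1−f) = R+W. The estimate is then right for women who live or work in Cabinda and too high for residents. If coverage differs between the groups, it is right for neither.

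**Recruitment**

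Let r be the share of coupons returned and q the share passed to Luanda residents (both assumed). With three coupons each, eligible recruits per participant are 3r(1−q), and chains shrink when this falls below 1, that is, when q > 1 − 1/(3r).

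- r = 0.5: shrinks once q > 1 − 1/1.5 = 0.33.
- r = 1.0: shrinks once q > 1 − 1/3 = 0.67.
- q = 1 (every coupon passed as scripted): no eligible recruits at any r. Only seeds remain, and Section VIII.A excludes their data.

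**The case against.** **The Luanda wording looks like a carry-over.** The site is a Cabinda health centre, the coupon carries its address, and screening would soon reveal a run of ineligible arrivals. This stands as a reason to treat complete recruitment failure, which a reader might infer, as the worst case under literal compliance and not as the expected result. It does not excuse the wording. This is the only coupon script in the protocol, and it concerns people paid for sex. The only planned RDS sample is the one in Cabinda, so the contingency plan for RDS among MSM and transgender women does not explain it.

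**The target may not be residents.** The size-estimation section speaks of sex workers in the province, not of residents. This stands in part: the bias is upward only relative to residents. Residents are, however, the population that Section VI.B and the inclusion criteria define, and the Data Collection paragraph refers to objects given to eligible women.

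**The size is hypothetical.** This stands. Only women living outside the province altogether count towards f, and nothing in the protocol supports any particular value.

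**Coordination is promised.** The Assumptions paragraph does say that definitions will be aligned and violations of the inclusion assumption reported. A general promise does not cure a specific instruction that contradicts it. Nor could the effect be removed afterwards, because item 5 of the log records a single yes or no.

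**Two stronger readings fail.** A reader might infer that the Luanda wording also inflates N. It does not, because Luanda residents are screened out before they can enter n2. A reader might also infer that network sizes are collected for the wrong population. The script governs handing out coupons, and Appendix 5, the Cabinda questionnaire, appears only as a heading, so its network question cannot be judged.

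**Conclusion.** The concern holds as two distinct inconsistencies, both to be corrected before training.

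- The coupon script contradicts the survey's residence criterion. Followed as written, it sends coupons to ineligible people. How far chains stall depends on compliance and coupon return, neither of which the protocol gives.
- The object-log instructions contradict both the printed log and the survey criterion, and breach the common catchment that the protocol itself requires. Relative to resident sex workers, N is inflated by 1/(1−f). This rests on a survey that represents residents and on an assumed f. It is zero if staff apply the printed log, and it is not a bias if the intended target is women who live or work in Cabinda and object coverage is equal in both groups.

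The documents do not establish an actual amount of inflation; they establish the mechanism and its direction relative to residents.

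**What to change.** 1. In Peer Recruitment and Survey Participation, replace Luanda with Cabinda province, and match the age wording to the inclusion criterion (at least 15).
2. Use one residence rule in the printed log, its instructions and the RDS inclusion criterion. Either keep residents only, so that item 5 asks whether the woman lives in Cabinda province, or admit women who live or work there in both the log and the survey. Fill in the blank place name on the log.
3. State in the size-estimation section which population N targets.
4. As a separate item, reconcile the age stops. The printed log refuses the object under 18 and its instructions under 15, while the survey admits women from 15.

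The cost is wording in one paragraph and one field form, plus one sentence on the target. Choosing live-or-work would also change the inclusion criterion. No sample size or analysis method changes.

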### **Coupon**

Each coupon will be uniquely coded in order to link seeds with new individuals in their recruitment chain. Each coupon will have an identifying code of the recruiter and a unique code for new recruitments, allowing us to

track social networks. Names and other personal identifying information will not be collected on any of the study forms. The coupons will be produced in such a way as to make them difficult to reproduce.

The coupon will consist of two parts and each part will bear an identical recruiter code. When the recruiters invite a new person they must hand over one of the parts of the coupon to the new recruited person, with the other part being kept by the recruiter. When the recruiters come back for their incentives, they must hand over their half of the coupon, which must match the half handed out to the new participants. In this manner the participants will remain anonymous, no names or personal identifying information will be collected on any study form.

Coupons will have the following elements:

- ID number (coupon number)
- Survey name (the target population and exact purpose will not be mentioned)
- Interview site address
- Telephone number of interview site
- Days and hours of operation
- Activation date: Date before which the coupon may not be used for enrolment. This date may vary; initially, the activation date will be two days after the coupon's issuance date. At the discretion of the study coordinator or the PI, recruits presenting coupons before the activation date may be accepted.
- Expiration date: Date after which coupon should not be used. Initially, coupons will be valid for two weeks. This time period may be extended or shortened if coupon return rates are below or above expectation and as the sample size approaches the target. At the discretion of the study coordinator or the PI, recruits with coupons that are within a set period of days past the expiration date may still be accepted.
- Information about its use and validity

A coupon may be invalid if: expired, tampered with, unreadable, or already used. Invalid coupons will be retained and stamped "VOID." Valid coupons of recruits undergoing screening for eligibility will be retained and stamped "USED." Recruits who are re-scheduled for a future visit will have their coupons returned to them. Re-scheduled visit dates may be past the coupon expiration date without rendering the coupon invalid.

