### ***Incentives***

MSM, transgender women and female sex workers that participate in the peer referral study (RDS), whether they are the initial "seeds" or a subsequent recruit, will receive mobile phone credit or other gift worth 900 Angolan Kwanzas (9 USD). The participant must consent to completing the survey and undergoing HIV and STI testing in order to be eligible for any amount of the incentive. If they subsequently refuse the HIV test and/or do not complete a majority of the questionnaire, they will not receive any incentive.

If an RDS participant successfully recruits one additional person to participate, they will receive an additional mobile phone credit or other gift worth 400 Angolan Kwanzas (4 USD) beyond the primary incentive, for a total incentive worth 1300 Kwanzas (~13 USD). If s/he recruits two additional persons to participate, s/he will receive an additional phone credit or gift worth 800 Kwanzas beyond the primary incentive, for a total incentive of 1700 Kwanzas (~17 USD). If s/he recruits three additional persons to participate, he will receive an

additional 1200 Angolan Kwanzas (~12 USD) beyond the primary incentive, for a total of 2100 Kwanzas (~21 USD).

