### **Collection of biologic specimens and testing**

All participants will be tested for HIV using a rapid test through finger prick blood sample at the health center study site. Participants will be offered syphilis, Hepatitis B, and Hepatitis C testing based on the SADC protocol. Nurses will collect venous blood for STI testing and provide results when participants return to the study site on a later date.

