#### **BIOBEHAVIORAL SURVEY IN CABINDA**

**Instructions:** Collect this information face-to-face from returning recruiters each time they come to collect their compensation.

**Oral consent script:** I am going to ask you a few questions about the people you tried to recruit with your coupons for this survey. We ask because we are especially interested in knowing about people who say they do not want a coupon. I do not want to know anyone's name, not even yours, for these questions. May I continue?

Coupon Identification Number: |\_\_|\_\_|\_\_|\_\_|\_\_|\_\_|\_\_|\_\_|\_\_|\_\_|

Name of Interviewer: \_\_\_\_\_ Date of Interview: \_\_\_\_\_

1. Is this the first time you have been here to collect compensation? Yes\_\_\_\_\_ No\_\_\_\_\_

If yes, continue. If no, answer questions for the period of time between when the subject was last here and filled out this same questionnaire and now.

2. How many coupons did you give out? \_\_\_\_\_ (Between the last time you came here to receive compensation and now).

3. How many people refused to accept coupons? \_\_\_\_\_ (if zero, skip to question 5. If > zero, continue)

4. These questions are asked for each individual who refused to accept the coupon.

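### The RDS non-response form is planned only for recruiters returning for a success-based payment, so refusal data come from a group selected on recruitment success and the recorded refusal rate is probably too low

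*Protocol*

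**What the plan says.** Three parts of Protocol section VI.D and one appendix fix the procedure.

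- **Timing in the body** (Peer Recruitment and Survey Participation): "After distributing their invitations to their peers, participants will return to collect their secondary incentives and will be asked to complete a non-response assessment". Each participant is told to "give one coupon to each of three friends, relatives or people they are close to".
- **Timing on the form** (Appendix 6): "Collect this information face-to-face from returning recruiters each time they come to collect their compensation". Its script gives the purpose: "We ask because we are especially interested in knowing about people who say they do not want a coupon".
- **Payment condition** (Incentives): "If an RDS participant successfully recruits one additional person to participate, they will receive an additional mobile phone credit or other gift worth 400" Kwanzas. Two recruits earn 800 and three earn 1200. Nothing is listed for a recruiter with no enrolled peer.
- **Proof for payment** (Coupon): "When the recruiters come back for their incentives, they must hand over their half of the coupon, which must match the half handed out". A match therefore needs an enrolled peer.

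Another return visit is planned but not linked to the form. Nurses take venous blood for STI testing and "provide results when participants return to the study site on a later date" (Collection of biologic specimens and testing).

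**The concern.** The form exists to learn about refusals, yet its only planned occasion is a visit that depends on at least one peer having accepted and enrolled. Enrolment is less likely the more peers refuse, so inclusion in the assessment depends on the outcome being measured. Question 6 of the form, on coupons the respondent herself turned down, goes to the same selected group.

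What is at stake is how non-participation in Cabinda will be described. A low refusal rate could be read as reassurance when part of it comes from whom the form reached. Forms never administered cannot be recovered in analysis, so this has to be settled in the field procedure.

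**Working it through.** The protocol states no refusal rate, so there is no figure to reproduce. The payment schedule is consistent: 900 + 400k gives 1300, 1700 and 2100 Kwanzas for k = 1, 2, 3, and no secondary payment for k = 0.

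**Inputs from the protocol.** About 400 women in Cabinda (section VI.E); three coupons each; payment only for enrolled peers.

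**Assumed inputs.** Refusal probability per offer, r; probability that a woman who accepts enrols, q; one offer per coupon; independent offers.

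**Step 1: recruiters with no enrolled peer.** About 400 women produce about 400 enrolments, so on average roughly one of each woman's three coupons is redeemed. With independent coupons:

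- P(no recruit) = (1 − 1/3)^3 = (2/3)^3 = 0.296
- 0.296 × 400 ≈ 119 women

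**Step 2: recorded refusal rate.** Let s = (1 − r)q be the chance that one offer ends in enrolment. The form is completed only if at least one of three offers succeeds, so

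- share not assessed = (1 − s)^3
- recorded rate = r × [1 − (1 − s)^2] / [1 − (1 − s)^3]

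With r = 0.30 and q = 0.5:

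- s = 0.7 × 0.5 = 0.35, which implies 3 × 0.35 = 1.05 recruits per woman, compatible with reaching the target
- share not assessed = 0.65^3 = 0.275
- recorded rate = 0.30 × (1 − 0.4225)/(1 − 0.2746) = 0.239

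**Step 3: who is left out.** In the unassessed group the refusal rate per offer is r/(1 − s) = 0.30/0.65 = 0.46. Recombining, 0.275 × 0.46 + 0.725 × 0.239 ≈ 0.30, the true value. Recruiters refused by all three peers are only 0.3^3 = 2.7% of all recruiters (about 11 of 400), or 0.027/0.275 ≈ 10% of the unassessed. The other unassessed recruiters had at least one peer who accepted but did not come.

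**Step 4: range.** The ratio of recorded to true rate depends only on s.

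| Case | s | Recruits per woman (3s) | Recorded rate relative to true |
|---|---|---|---|
| r = 0.1, q = 0.7 | 0.63 | 1.89 | 9% too low |
| one in three redeemed | 0.333 | 1.00 | (5/9)/(19/27) = 0.789, 21% too low |
| r = 0.4, q = 0.3 | 0.18 | 0.54 | 27% too low |

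The last row could not sustain recruitment to 400, so the middle row is the most relevant one.

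**Step 5: departures from the model.** If refusal varies between recruiters (beta distribution, concentration 4, an assumption), simulation with mean refusal 0.30 and q = 0.5 gives a recorded rate of 0.20. If every refused coupon is re-offered until all three are accepted, and recruiters are alike in refusal, simulation gives 0.30 for a true 0.30, so no bias: whether a peer enrols then no longer depends on how many refused.

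**The case against.** **Re-offering.** This is the strongest point against a fixed size. A refused coupon stays with the recruiter, and Appendix 6 has four columns for refusers and three for accepters, so more than three approaches are foreseen. Re-offering shrinks the bias, to nothing in the limiting case above. This stands. It limits what can be said about magnitude, and a reader who infers an understatement of known size goes beyond the documents.

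**Attendance is not forbidden to unsuccessful recruiters.** The body text is worded as if all participants return, and the incentive rule restricts payment, not attendance. So it is too strong to say such women can never be asked. Still, both the body and the form name only the compensation visit, and a woman with no enrolled peer has nothing to collect there.

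**Other information on recruitment.** A reader might take this form as the only evidence on who is missing. It is not. The coupon database tracks coupons and recruits for all participants (section VII.B), recruitment is monitored for bottlenecks (section VI.D), and homophily and recruitment patterns are examined (section VIII.A). None of these, however, separates a refused coupon from one accepted and not used, or gives reasons.

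**Downstream use.** A reader might also infer biased HIV prevalence or population size. The documents do not support that: refusals enter neither the RDS adjustment in section VIII.A nor the multiplier formulas in section VIII.C. For refusers the form records only relationship, length of acquaintance and reason, so even complete forms would say little about bias in prevalence.

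**Question 6.** Only the title of the Cabinda questionnaire (Appendix 5) is in the document, so it cannot be judged whether the main interview already asks about refused coupons.

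**Conclusion.** The concern holds in a limited form. As written, the form reaches recruiters selected on having at least one enrolled peer. About 30% of recruiters would have no planned occasion to be asked, if one coupon in three is redeemed independently. The recorded refusal rate is likely too low: 24% instead of 30% under the assumed values with one offer per coupon, less with re-offering, more if refusal differs between recruiters and coupons are not re-offered. The true refusal rate, and so the actual bias, cannot be found from the protocol.

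It would be wrong to describe the omitted group as recruiters whose peers all refused; under the same values they are about a tenth of it. The damage is confined to the descriptive non-response assessment. That makes it worth correcting because it is cheap, but it is no threat to the main estimates.

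**What to change.** - Amend Peer Recruitment and Survey Participation in section VI.D and the Appendix 6 instruction so that the form is given at every return visit, for compensation or for STI results, including to women with no enrolled peer.
- Keep the form's logic of asking about the period since the previous visit, so that later refusals accumulate. Questions 1 and 2 should refer to the last visit of either kind, not the last payment. Using only the first return would lose refusals that occur after it.
- Ask question 6 of all participants at the main interview, unless the Cabinda questionnaire already does.
- Report the number of recruiters assessed out of all those given coupons, beside the refusal rate, and take coupon redemption from the coupon database.

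The cost is a wording change in two places, one question in the main interview and slightly longer results visits. Women who never return are still missed, so the assessed share needs reporting even after the change.
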